#### Withdrawal criteria and management

Withdrawal or dropout criteria:

1. At the participants’ own request or that of the legal representative.

2. Participants who develop a serious disease, such as heart disease or pneumonia and, in the investigator’s opinion, it is not suitable to continue.

3. The participant’s compliance is poor, in the investigators’ opinion,and it is not suitable that they should keep taking part in the research.

4. The participants have an adverse reaction related with acupuncture treatment.

Withdrawn subjects or dropouts should be managed as follows. Details of the withdrawn patients should be documented in the ‘clinical trial performance forms’ in the case report files (CRF) of the patients. Details of patients who have withdrawn as a result of an adverse event or reaction should be recorded in the CRF. If the patients who have been determined as dropout or withdrawn cases require further treatment, the investigators should provide the treatments; however, their data will be treated as missing data.Details of all withdrawn patients will reported in the final results, to guarantee maximum transparency.

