#### Sample size calculation

The sample size calculation is based on the two-sided chi-square test for difference with respect to the primary endpoint. There are few reports in the literature of clinical trialsof acupuncture treatment for depression insomnia. Based on our earlier randomized controlled pre-trial in Guangdong Provincial Hospital of TCM, we decided to adapt the reduction of the HAMD and PSQI scores as a baseline for the sample size calculation for our trial. We believe that the successful cure rate for depression insomnia is approximately 40% when adopting the conventional acupuncture formula and should be increased to 70% or more when using the optimized acupuncture formula. A sample size of 58 patients per group is necessary (as calculated using PEMS version3.1 software,with the predicted cure rates of 40% and 70%). The maximum dropout rate within the intervention is expected to be about 15%. Therefore, another 24 patients in total have to be randomized to obtain the required number of patients. The total number of patients needed to be randomized is therefore 140.

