#### Study treatment

The patients taking part in the study will each receive 24 acupuncture sessions (twice per week), either conventional or optimized, as follows.

The treatment will be performed after sterilizing the skin on the acupuncture point areas and with patients lying face up. The temperature of the treatment room is not lower than 25°C.

1. Conventional acupuncture treatment

All the patients in intervention group 1, the control group, will receive the conventional acupuncture formula at the following points: LI-4 (He Gu), LIV-3(Tai Chong), EX-HN-3 (Yin Tang), and GV-20 (Bai Hui). The needles, size 0.35 × 25 mm,are produced by Suzhou Tianxie Acupuncture Instruments Co., Ltd. The needle are maintained in the acupuncture points for 30 minutes. During the treatment, after a De Qi sensation is produced, which is described as a numb, distended and aching sensation, patients are required to take six deep breaths and then have a rest, followed by another six deep breaths every minute until the needles are removed.

2. Optimized acupuncture treatment

The basic treatment formula is modified. On the basis of the normal acupuncture, LU-7 (Lie Que) and KID-6 (Zhao Hai) are added and needles remain in the body after patient feels the De Qi sensation. The embedded needles are then buried, for two groups of points (1) Bl-15 (Xin Shu), Bl-23 (Shen Shu), and Bl-19 (Dan Shu), N-HN-54 (An Mian); these two groups of points are used alternately. The granular type of embedded needle used has a needle tip of about 2 or 3 mm and is manufactured by Suzhou Medical Instrument Factory, China. The needle is inserted perpendicularly underneath the skin and is fixed with 3M medical proof fabric. Before the start of the next treatment, the embedded needles are removed.

To minimize treatment bias, all the acupuncturists who participate in this trial are acupuncturists of a general acupuncture department and each research center. They all gained medical licenses in China and were well trained according to the trial’s procedure under the guidance of senior acupuncturists.

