### Common acupuncture adverse events or reactions and processing

#### Common acupuncture adverse events or reaction

1. Needle fainting during acupuncture treatment

For patients who are on their first visit or have a serious phobia about needles, a reassuring explanation is necessary. The patient’s complexion will be closely observed to check for any early symptoms of needle fainting, such as discomfort, dizziness, pale face, tiredness, sudden cold sweat, cold limbs, weak breathing, pale and green complexion, blue lips, low blood pressure, or obnubilation. If these symptoms occur, the needles should be removed as soon as possible. The patient is then kepthorizontal with feet slightly raised, and offered warm sugar water. If the symptoms are serious, DU-26 (Shui Gou), DU-25 (Su Liao), PC-6 (Nei Guan), and ST-36 (Zu San Li) points are selected as emergency points. If the symptoms persist, other professional hospital emergency measures may need to taken.

2. Convulsions

All acupuncturists must determine whether the participants have a history of convulsion.If a patient has a convulsion history during acupuncture treatment, close observation is needed. The practitioner will remove all the needles and take some emergency measures. If the disease is not immediately controlled or the convulsions persist, the participants must be transferred to the emergency center immediately.

3. Severe pains

Severe pains during and after treatment are usually caused by improper needle manipulation or strong stimulation. If the pain is of low intensity, a local compress is used to stop the pain; if the pain is heavier, moxibustion can be applied.

4. Needle sticking

If needle sticking occurs, the patients will be required to relax. If the stickingis caused by twisting the needle inone direction, the problem is solved by rotating the needle in the opposite direction. If the sticking is caused by the over-contraction of the muscle, the needles are removed and the local area of the acupuncture points is pressed, where the needle is stuck, or another needle is placed in the local area, to distract the patients’ attention. If the situation occurs because of a change in the patients’ position, it will be relieved when the patient resumes the correct position.

5. Local infections

If a strict aseptic operation is ignored, local infection occurs. Once the infection is diagnosed, proper treatment will be needed or drug therapy is suggested.

6. Subcutaneous hematoma

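### Withdrawal criterion 4 covers any acupuncture-related reaction without the suitability judgement of criteria 2 and 3, so minor reactions can cause avoidable missing scores (minor)

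*Protocol article*

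**What the plan says.** **Protocol article, Withdrawal criteria and management.** Four grounds are listed. The first is a request by the participant or legal representative. Criterion 2 (serious disease) applies when, in the investigator's view, "it is not suitable to continue". Criterion 3 (poor compliance) applies when, again in the investigators' view, "it is not suitable that they should keep taking part in the research". Criterion 4 is only: "The participants have an adverse reaction related with acupuncture treatment". For withdrawn patients or dropouts who "require further treatment, the investigators should provide the treatments; however, their data will be treated as missing data".

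**Common acupuncture adverse events or reaction.** Needle sticking, bruising and pain get on-the-spot remedies, for example "If the pain is of low intensity, a local compress is used to stop the pain". The section does not say whether the patient then stays in the trial.

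**Assessment of adverse events or reactions.** For reactions other than those listed, the investigator weighs relatedness. One item is whether the reaction recurs on repeat needling, subject to the patient's safety and consent.

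**Study treatment.** There are 24 sessions, two a week. Only the optimized arm receives LU-7, KID-6 and embedded needles, which stay in between sessions: "Before the start of the next treatment, the embedded needles are removed".

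**Data storage and statistical analysis of the trial outcomes.** Intention-to-treat and per-protocol analyses are both planned, and missing data are filled with the last value.

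**Sample size calculation.** Cure rates of 40% and 70% are compared with a two-sided chi-square test. "A sample size of 58 patients per group is necessary". "The maximum dropout rate within the intervention is expected to be about 15" percent. The total randomized is 140.

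**The concern.** Pneumonia leads to withdrawal only after a judgement on whether the patient should continue. A bruise from a needle, on the literal wording, needs no such judgement. Three centres recruit, and criterion 4 gives them no common threshold.

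The statistical stake is the data lost after withdrawal. Losses under this criterion are treatment-related by definition. A patient withdrawn before the 1-month visit has only a baseline score to carry forward, which is recorded as no improvement. The optimized arm has more needling exposure, so unequal loss is plausible. In that case, baseline values carried forward would lower the apparent cure rate more in the optimized arm and bias the comparison against it.

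Carried-forward bias affects withdrawals under criteria 1 to 3 as well. What criterion 4 adds is withdrawals that need not happen.

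**Working it through.** **1. Wording side by side.**

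| Criterion | Ground | Judgement on continuing |
|---|---|---|
| 1 | Participant's or representative's request | Not applicable |
| 2 | Serious disease | Yes |
| 3 | Poor compliance | Yes |
| 4 | Acupuncture-related reaction | None stated |

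Nothing elsewhere in the article narrows criterion 4.

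**2. The plan's own figures.** Alpha and power are not stated; two-sided 5% is assumed throughout. Let p1 and p2 be the cure rates, p their mean, and d their difference.

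n per arm = [1.96·√(2p(1−p)) + z·√(p1(1−p1) + p2(1−p2))]² / d²

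With p1 = 0.40, p2 = 0.70, p = 0.55 and 90% power (z = 1.2816): (1.96 × 0.7036 + 1.2816 × 0.6708)² / 0.09 = 55.7, so 56. This is within two patients of the stated 58. Dropout: 116 / 0.85 = 136.5, so 137, close to 116 + 24 = 140. Neither figure is in dispute.

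Power = Φ{[d√n − 1.96·√(2p(1−p))] / √(p1(1−p1) + p2(1−p2))}

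At n = 58: (0.30 × 7.616 − 1.3790) / 0.6708 = 1.350, so power is **91.2%**. This is the reference below.

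**3. Illustration with equal loss.** All of the following is assumed: criterion 4 applied literally, the same reaction rate r per session in both arms, independent sessions, no other loss, and 70 patients per arm analysed with carried-forward values. Eight of the 24 sessions fall before month 1.

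- Total loss: L = 1 − (1−r)^24
- Loss before month 1: E = 1 − (1−r)^8
- Milder case: only withdrawals before month 1 count as not cured, so the cure rates are 0.40(1−E) and 0.70(1−E)
- Harsher case: all withdrawals count as not cured, so the cure rates are 0.40(1−L) and 0.70(1−L)

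For L = 15%: r = 1 − 0.85^(1/24) = 0.675%; 0.15 × 140 = 21 patients; E = 1 − 0.99325^8 = 5.27%, or 7.4 patients.

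- Milder: 37.9% vs 66.3%, power 92.9% (+1.7 points against 91.2%)
- Harsher: 34.0% vs 59.5%, power 86.4% (−4.8 points)

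| r per session | Total loss | Patients of 140 | Power, milder | Power, harsher |
|---|---|---|---|---|
| 0.25% | 5.8% | 8 | 94.5% | 92.6% |
| 0.675% | 15.0% | 21 | 92.9% | 86.4% |
| 1% | 21.4% | 30 | 91.5% | 81.1% |

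Power can exceed the reference because all 70 per arm are analysed, not 58.

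**4. Illustration with unequal loss.** Assume that a share e of would-be responders is withdrawn early in the optimized arm only and carried forward as not cured. The optimized cure rate becomes 0.70(1−e), against 40%, with 70 per arm.

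| e | Optimized cure rate | Power |
|---|---|---|
| 0% | 70.0% | 95.4% |
| 5% | 66.5% | 89.0% |
| 10% | 63.0% | 78.3% |
| 15% | 59.5% | 63.8% |

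The article supports none of these shares. The table shows only the direction, and that unequal loss costs more than equal loss.

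**The case against.** The strongest case on the other side has five parts.

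- **The list may be permissive.** It gives grounds and never says that every patient with a reaction must leave. A reader might infer that criterion 4 forbids continuing after a reaction. The text does not establish that, because the permissive reading is available. Even so, criterion 4 then gives no threshold where criteria 2 and 3 do.
- **Some judgement is involved.** A reader might infer that criterion 4 dispenses with judgement altogether. It does not: relatedness must be decided, and for reactions outside the listed ones it is an investigator assessment. That judgement concerns cause, not suitability to continue.
- **There is no contradiction.** The section on common events gives first aid and is silent on trial participation. The repeat-needling item belongs to a causality checklist for other reactions. These sections suggest that treatment can go on, but they do not say so. This stands: the fit is poor, but the texts do not conflict outright.
- **The missing-data link is uncertain.** The sentence can be read as covering only withdrawn patients who receive further treatment. This also stands.
- **The article condenses a fuller protocol.** Severity thresholds may be set out there. That is possible, but criterion 4 is a stated rule, and the qualifier is printed for its two neighbours.

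A reader might also infer that the trial lost material power or is known to be biased. No reaction rate is given for either arm, so the documents support neither.

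**Conclusion.** The point holds as a minor one. Criterion 4 allows, and read literally requires, withdrawal for any acupuncture-related reaction. Under that reading, minor reactions can produce avoidable, treatment-related missing scores that are then carried forward.

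The size is unknown. Under equal loss the assumed scenarios run from slightly above planned power to 81.1%. They fall below plan only when loss is 15% or more and every withdrawn patient counts as not cured. Unequal loss would matter more and would work against the optimized formula, but nothing in the article shows that it occurred. All figures rest on a two-sided 5% level and on reaction rates chosen for illustration.

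**What to change.** **Wording, were conduct still open.** Add to criterion 4, for both arms alike, that it applies when in the investigator's opinion "it is not suitable to continue". State that minor reactions managed on the spot do not end participation.

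**Data.** When needling stops for a reaction, keep the scheduled PSQI and HAMD assessments (months 1 and 2, and the planned end at 24 / 2 = 12 weeks). Use those scores in the intention-to-treat analysis instead of treating them as missing.

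**For the trial as concluded.** The Trial status section says that the project ended in 2011. Use any scores that were collected after withdrawal. Report criterion-4 withdrawals by arm, severity and last observed visit.

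**Cost.** During conduct: one clause, a memo to the sites, and assessments already on the schedule; no extra patients. The clinicians must agree the threshold, and some patients who stop needling will not return. For the concluded trial: one table, since the article already promises details of all withdrawn patients, plus re-entry of any scores that were set aside.

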### Hypothesis

Acupuncture is capable of reducing levels of depression, whether with a conventional treatment formula or an optimized treatment formula. Furthermore, optimized acupuncture is capable of reducing levels of depression insomnia, to a greater degree than conventional acupuncture formula. Meanwhile, the results of the optimized formula of acupuncture treatment for depression insomnia are supposed to increase the clinical efficacy of treating depression insomnia, improve the health-related life quality of depression insomnia patients, and moderate the consumption of drugs used in conventional treatment, eventually leading to significant social and economic benefits.

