### Data collection and outcome assessment

The data required for evaluating the effectiveness of the treatment will be collected at baseline, at the start of the treatment, 1 month after the treatment has begun, 2 months after the treatment has begun, and at the end of the treatment. The data required for the blind method cognitive evaluation will be collected after the second acupuncture treatment and after the last treatment.

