### Data storage and statistical analysis of the trial outcomes

The data compilation form containing the variables of interest will be completed by the corresponding researcher at each center. Data will be documented in the paper CRF by researchers or evaluators and will be double-checked by quality inspectors. The supervisor will inspect the progress of the trial at regular intervals in each branch center. All the detailed original data (paper CRF) will be recorded timely, clearly, and completely. The case reports will be modified only by researchers who are documenting the data. The correct method of modification is tomark a line through the original record and write the revised data next to the original data,so that the change may be clearly visible. The modified data will be documented with data and the initials of the investigator. All the materials will be kept for 5 years after the completion of the study. At each center, the information obtained will be recorded on an electric database by EpiData software 3.1 at the same time, for subsequent statistical analysis.

Predictive Analytics Software (PASW, version18.0) is used for data analyses. Exploratory analysis will include the minimum, maximum, median, mean, and standard deviation. For measurement data, a normality test is necessary. Furthermore, baseline categorical data, demographic characteristics, such as sex and age category, and numerical data are analyzed with chi-squaretests and one-way analyses of variance (ANOVA). Student’s *t*tests are used tocompare different periods of measurement data. Wilcoxon matched-pairs signed-rank tests are used for ranked data. Independent Student’s *t*tests and 95% confidence intervals are used to detect differences between groups of the measurement data only if the normality test and analysis of variancetestsprove significant, otherwise rank-sum tests should be used, which are also used to detect differences between groups of ranked data. Linear mixed models (for continuous outcome variables) and generalized estimating equations (for categorical outcome variables) are used to examine changes over time and the severity of PSQI and HAMD. Both intention-to-treat and per-protocol analyses are used. Data from participants who do not violate the treatment protocols will be included in the per-protocol analysis. Missing data are dealt with using the ‘last value carried forward’ method.

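### Last value carried forward, the only missing-data rule stated, lets a score about 4 to 12 weeks old stand as the end-of-treatment result in the intention-to-treat analysis

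*Protocol article*

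**What the plan says.** All references are to the protocol article.

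- **Data storage and statistical analysis of the trial outcomes.** Missing data are handled by "last value carried forward". No other rule is given. On the analysis sets: "Both intention-to-treat and per-protocol analyses are used". On longitudinal models: "Linear mixed models (for continuous outcome variables) and generalized estimating equations (for categorical outcome variables) are used to examine changes over time". The text does not say whether those models use observed or filled scores.
- **Withdrawal criteria and management.** For withdrawn patients who need further care, "the investigators should provide the treatments; however, their data will be treated as missing data". One listed reason for withdrawal is: "The participants have an adverse reaction related with acupuncture treatment".
- **Data collection and outcome assessment.** Effectiveness data are collected at baseline or the start, then "1 month after the treatment has begun, 2 months after the treatment has begun, and at the end of the treatment".
- **Study treatment.** There are 24 sessions, two a week. Only the optimized arm has needles left in place between sessions: "Before the start of the next treatment, the embedded needles are removed".
- **Hypothesis.** "Acupuncture is capable of reducing levels of depression, whether with a conventional treatment formula or an optimized treatment formula".
- **Sample size calculation.** Dropout is put at a maximum of about 15%, and 140 patients are to be randomized.

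**The concern.** Carrying the last score forward treats a patient's state at the last visit as the state at the end of treatment. In a trial that expects scores to fall in both arms, this contradicts the plan's own hypothesis. A patient who leaves before month 1 is analysed at week 12 with the score that met the entry criteria (HAMD above 20, PSQI of 7 or more). The filled value is then treated as if it had been observed.

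The error for a single patient can go either way. A patient who would have improved is frozen too high, and one who deteriorates after the last visit is frozen too low. Both primary outcomes are exposed. A true difference that builds up over time is diluted, and if the arms lose patients at different rates, a difference can appear between equally effective treatments.

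**Working it through.** **Inputs from the article.** 24 sessions at 2 per week; visits at the start, month 1, month 2 and end; maximum dropout about 15%; 58 per group before dropout; 140 randomized, 1:1.

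**The plan's own total.** 2 × 58 = 116, and 116 + 24 = 140. Allowing for 15% loss gives 116 / 0.85 = 136.5, or 137, so 140 is consistent with the stated ceiling.

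**Age of the carried score.** Treatment lasts 24 / 2 = 12 weeks. Taking a month as 4 weeks:
- last score at the start: 12 − 0 = 12 weeks old
- last score at month 1: 12 − 4 = 8 weeks old
- last score at month 2: 12 − 8 = 4 weeks old

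Calendar months give about 7.7 and 3.3 weeks for the last two, which changes nothing of substance.

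**Patients affected.** At most 0.15 × 140 = 21, or 0.15 × 70 = 10.5 per arm.

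Everything below rests on assumptions, because the article gives no expected fall, SD, correlation, dropout timing or imbalance.

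**Share of the change missed.** Assume linear change and dropouts spread evenly over the three intervals. The carried score misses (3/3 + 2/3 + 1/3) / 3 = 2/3 of the change.

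**Balanced dropout.** With 15% in each arm and no true difference, the expected shift is zero. A true difference that grows linearly to D is estimated as D × (1 − 0.15 × 2/3) = 0.90 D, a loss of 10%.

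**Unequal dropout, no true difference.** Shift = gap in dropout × 2/3 × fall in HAMD.
- 12.5% v 17.5%, fall of 8 points: 0.05 × 5.33 = 0.27 points
- 10% v 20%, fall of 12 points: 0.10 × 8.0 = 0.80 points

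The arm that loses more patients looks worse.

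**Simulated t tests at a two-sided 5% level.** 70 per arm, no true difference, correlation 0.5 between scores a month apart, dropout unrelated to scores. The table gives rejection rates for carried-forward scores.

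| Dropout | Fall, SD | Fixed dropout counts | Dropout random per patient |
|---|---|---|---|
| 10% v 20% | 12, 6 | 8.0% | 10.6% |
| 12.5% v 17.5% | 8, 8 | 4.8% | 5.5% |
| 15% v 15% | 12, 6 | 2.9% | 4.9% |

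In the two unequal settings, generalized least squares on the observed scores (covariance taken as known) gave shifts within 0.03 points and rejection rates of 5.2% and 5.5%.

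**Direction.** With 10% dropout in the conventional arm, 20% in the optimized arm and random dropout, a separate run rejected in 10.7% of trials. Of all trials, 10.2% favoured conventional acupuncture and 0.5% favoured optimized, against a nominal 2.5% on each side.

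**The case against.** **The withdrawal clause may say little.** It concerns patients who go on to further care, and it most naturally means that scores under that care are not trial data. A reader might infer that a withdrawn patient's whole record is discarded. The article does not support that, because carrying a value forward needs the earlier scores to be kept. This objection stands, so the point rests on the statistical section.

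**Mixed models and generalized estimating equations are already planned, and an unseen analysis plan may settle which values they use.** This is fair as far as it goes. But the article publishes the carry-forward rule without exempting those models, and fitted to filled data they lose their advantage with incomplete records. This is a weak rule stated in the text, not a missing detail.

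**The size is small and assumed.** Largely true. The 15% is a ceiling, both unequal scenarios put one arm above it, and only the more extreme one clearly raises the error rate.

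**The bias would not flatter the new treatment.** A reader might infer that the rule could manufacture a benefit for optimized acupuncture. The only arm-specific mechanism the article suggests is more adverse-reaction withdrawals where needles stay embedded. With scores falling, that would count against optimized acupuncture. Even this is inference, since the article ties none of its listed complications to embedded needles. The objection stands on direction. It does not remove the dilution of a true effect.

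**Conclusion.** The concern holds in a limited form. The article fixes a missing-data rule that conflicts with its own expectation of improvement and lets a score about 4, 8 or 12 weeks old serve as the end-of-treatment result. The scores' ages and the ceiling of 21 of 140 patients follow from the document.

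The rest is conditional. Under even dropout timing and a linearly growing effect, balanced 15% dropout costs about 10% of the true difference and creates no false one. A gap of 5 to 10 percentage points in dropout moves the HAMD comparison by about 0.3 to 0.8 points for assumed falls of 8 to 12. The article cannot establish whether dropout was unequal or in which direction any shift went. The rule is worth changing because a better analysis is already in the plan, but the article does not show that it would invalidate the result.

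**What to change.** 1. **Statistical section.** State that the intention-to-treat analysis of HAMD and PSQI fits the planned linear mixed models to all observed scores in the assigned group, with no values carried forward. Keep the carry-forward analysis as a sensitivity analysis only.
2. **Cure rate.** Add a sensitivity analysis that counts patients without an end-of-treatment score as not cured.
3. **Withdrawal section.** Clarify only that scores recorded before withdrawal are kept and analysed.

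The cost is wording and analysis time: the models are already planned and the scores already recorded, so no visit or form is added.

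There are downsides. The mixed model assumes that missingness depends on observed scores, so it cannot recover a deterioration that was never scored. Counting dropouts as not cured lowers both rates. If all 15% would otherwise have had the planned cure rates, 40% v 70% becomes 0.85 × 40 = 34% v 0.85 × 70 = 59.5%, and the difference falls from 30 to 25.5 points. That is why it belongs among the sensitivity analyses. Because the trial concluded in 2011, the change must be labelled as made after the original plan.
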